### Sample size

Power calculations were performed using the methods of Julious et al. [49], for paired binary comparisons and Hayes et al. [50] for community randomised trials. We assumed that the prevalence of CT and/or NG will be 15% at recruitment to the trial in each year, that 30% of patients will have a positive re-test within three months (in the standard practice phase), and that at least 150 patients aged 16–29 years will be tested at each health service in both POC and standard practice years. Table 2 shows the total number of health services needed to detect a reduction in CT and NG repeat positivity rate from 30% in control health services to 15% in intervention health services with 80% and 90% power, differing community coefficients of variation (0.25, 0.30) and equal numbers of health services in each arm. At least ten services will provide data in both the intervention and control arms. This will ensure 88% power to detect a decrease in CT and NG repeat positivity rate from 30% to 15%, and 78% power to detect a reduction from 20% to 10%. Conservatively, 12 services will be included in the trial.

**Table 2 T2:** Sample size estimates based on reduction in repeat positivity rate from 30% to 15%

**Coefficient of variation**	**Number of services**	
	**80% power**	**90% power**
25%	8	10
30%	10	14

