In regional and remote areas, primary health services play an important role in the prevention, testing, treatment and management of CT and NG. These health services are either State or Territory government funded or Federal government funded Aboriginal Community Controlled Health Services (ACCHS) and are the primary health care provider for Aboriginal people. There are an estimated 150 ACCHS located across Australia. Current clinical practice in most remote Aboriginal communities [13-15] follows guidelines which provide for immediate treatment if NG or CT are suspected on the basis of specified symptoms or risk [16]. Although symptom-driven diagnosis has the advantage of providing a rapid pathway to treatment, it has poor sensitivity and specificity for detecting infection, particularly in women [17,18]. Used as a diagnostic strategy on its own it therefore leaves many infections untreated, and results in unnecessary treatment in others.

As CT infections are mainly asymptomatic, and NG infections are mainly asymptomatic in women and in about 50% of men [19-21], treatment and contact tracing is usually initiated once a specimen has been tested and found positive by the laboratory. Treatment for these infections is almost inevitably delayed due to a range of factors including the time taken to transport the specimen from remote health services to laboratories [22], and delays in recalling patients when a positive diagnosis occurs. Some health services are more than 1000 kilometers away from the laboratory and pathology is sent on a weekly basis by small plane. A recent review of STI programs in remote Aboriginal communities showed that in a 12 month period only 75-89% of people diagnosed with an STI were treated, and the average time from diagnosis to treatment in asymptomatic people was 21 days [23] , far longer than the 2–3 day interval experienced in most urban settings [24].

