### Identification of communities and health services and eligibility criteria

In the first instance, potentially eligible health services will be identified in consultation with Government and Aboriginal Community Controlled Health Organisations. Identified health services will then be approached and invited to participate in TTANGO if they meet the following inclusion criteria: located in communities classified as regional, remote or very remote by the Australian Bureau of Statistics [41]; annually offer CT and NG testing to a minimum of 150 people aged 16–29 years (see sample size section), with a CT and NG positivity of at least 10% in 16–29 year olds; agree to be randomly assigned in one year out of two to the POC phase; have an electronic patient management system; and have the staff and resource capacity to fulfil protocol requirements.

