## Discussion

Rates of CT and NG in remote Aboriginal communities in Australia are unacceptably high, and TTANGO will evaluate whether POC testing for these STIs can improve the timeliness of treatment and in turn reduce repeat infection rates. To our knowledge, TTANGO will be the first randomized trial of molecular POC tests for CT/NG infection internationally.

It is anticipated that one of the main challenges for TTANGO will be to sustain the involvement of health service staff amidst the numerous competing demands and health priorities, and also ensure POC operator competency is maintained in the context of high staff turnover. Regular communication and training with trial sites from a dedicated TTANGO coordinator should help to mitigate this risk. Another challenge will be if the services randomised to the POC arm in the first year prefer to keep the POC machines due to realized improvements in STI management. In the consultation phase we emphasized to health services the importance of the cross-over design to ensure long term policy change and funding. Finally, repeat positivity rates are calculated from those who re-tested and these need to be similar in both POC and non-POC arms to minimize biases – lower re-testing rates are often associated with higher repeat positivity due to re-testing in those with symptoms [53]. To mimimise any imbalance in re-testing rates, a quality improvement program and incentives associated with re-testing have been provided in both arms.

This research is significant as study outcomes will make an important contribution to the international understanding of STI control using POC tests. The research may also lead to significant decreases in STI prevalence and reinfection across multiple sites with long term benefit for the sexual health and wellbeing of young Aboriginal people. Finally, it has the potential to influence public health policy and result in [54] uptake of CT and NG POC tests into further remote clinical services in Australia, and other settings.

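### The 88% and 78% power stated for ten services leaves no stated allowance for infected patients who are not treated or not re-tested, so it is not ensured

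*Protocol article*

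**What the plan says.** The Sample size section of the protocol article lists its inputs:

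- "at least 150 patients aged 16–29 years will be tested at each health service in both POC and standard practice years";
- "the prevalence of CT and/or NG will be 15% at recruitment to the trial in each year";
- "30% of patients will have a positive re-test within three months (in the standard practice phase" and half of that under point-of-care (POC) testing;
- a between-service coefficient of variation (CV) of 0.25 or 0.30.

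For ten services it concludes: "This will ensure 88% power to detect a decrease in CT and NG repeat positivity rate from 30% to 15" per cent, and "78% power to detect a reduction from 20% to 10" per cent. It then enrols 12 services as a conservative choice.

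Two other sections settle who is counted. Outcome measures defines repeat positivity at three months after treatment. The Discussion says that "repeat positivity rates are calculated from those who re-tested". The Sample size section gives neither a treated share nor a re-tested share, and does not state alpha, sidedness or which CV lies behind the two power figures.

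**The concern.** A patient enters the primary outcome only if infected, treated and re-tested. The stated inputs stop at infected. Unless an allowance was made and not reported, the power was computed on a denominator larger than the one the outcome will have.

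The article itself expects loss. The Background reports that in earlier remote programmes "only 75-89% of people diagnosed with an STI were treated". The STI quality improvement section reports the percentage re-tested back to each site. The Clinical performance incentives section pays per re-test. The Discussion treats low re-testing as a source of bias.

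What is at stake is how a null result would be read. If the power is taken as guaranteed, such a result counts as good evidence that POC testing does not halve repeat positivity. If many infected patients are not re-tested, that inference is weaker than the article implies.

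**Working it through.** **Inputs.** From Sample size: 150 tested, 15% infected, 30% v 15% and 20% v 10% repeat positive, c = 10 or 12 services, CV k = 0.25 or 0.30. Assumed because not stated: alpha 5%, one- or two-sided, and a small-sample correction d of 0 or 1 cluster. The treated-and-re-tested share f is not given, so it is varied.

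**Denominator.** 150 × 0.15 = 22.5 infected per service-year, and n = 22.5 × f.

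**Formula** (CV form for community-randomised trials, the two years taken as independent):

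V = p0(1−p0)/n + p1(1−p1)/n + k²(p0² + p1²)

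power = Φ( √(c−d) × (p0−p1)/√V − z )

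**Reproducing the stated figures, c = 10, f = 1 (n = 22.5).**

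Setting A: two-sided (z = 1.96), k = 0.25, d = 0.
- 30% to 15%: V = 0.21/22.5 + 0.1275/22.5 + 0.0625 × 0.1125 = 0.02203; power = Φ(3.196 − 1.96) = 89.2%.
- 20% to 10%: V = 0.16/22.5 + 0.09/22.5 + 0.0625 × 0.05 = 0.01424; power = Φ(2.650 − 1.96) = 75.5%.

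Setting B: one-sided (z = 1.645), k = 0.30, d = 1.
- 30% to 15%: V = 0.02513; power = Φ(2.839 − 1.645) = 88.4%.
- 20% to 10%: V = 0.01561; power = Φ(2.401 − 1.645) = 77.5%.

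Setting B matches both printed figures and A comes close. Using all 150 tested patients as n gives about 95% or more in every setting tried, so the calculation did use the infected subset. In B, ten services need n = 22.0 for 88% and n = 22.9 for 78%, that is 98% and 102% of 22.5. That leaves no room for loss.

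**Power (%) by f, shown as 30% to 15% / 20% to 10%.**

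| f | n | A, 10 services | B, 10 services | A, 12 services | B, 12 services |
|---|---|---|---|---|---|
| 1.00 | 22.5 | 89.2 / 75.5 | 88.4 / 77.5 | 93.8 / 82.7 | 93.2 / 84.4 |
| 0.89 | 20.0 | 86.6 / 71.6 | 86.3 / 74.4 | 92.0 / 79.2 | 91.7 / 81.6 |
| 0.75 | 16.9 | 82.3 / 65.6 | 82.8 / 69.6 | 88.5 / 73.4 | 88.9 / 77.1 |
| 0.50 | 11.25 | 69.3 / 51.0 | 72.6 / 57.5 | 77.0 / 58.5 | 79.9 / 65.0 |
| 0.30 | 6.75 | 51.0 / 35.1 | 57.5 / 43.1 | 58.5 / 40.8 | 65.0 / 49.3 |

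The 0.89 and 0.75 rows correspond to the treated range quoted in the Background if every treated patient were also re-tested.

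**Share that 12 services need to keep the stated figures.** For 88% (30% to 15%): n = 16.5 in A and 16.1 in B, so f = 73% and 71%. For 78% (20% to 10%): n = 19.3 and 17.4, so f = 86% and 78%.

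**Limits of the reproduction.** Two-sided with d = 1, even f = 1 gives only 85.8% / 71.0% (k = 0.25) or 81.0% / 67.0% (k = 0.30) with ten services. In the other direction, one-sided with k = 0.25 and d = 1 reaches the printed figures at n = 18.3 and 20.4, and one-sided with k = 0.30 and d = 0 at n = 18.6 and 19.8. One-sided with k = 0.25 and d = 0 does so at n of about 17. No single setting at n = 22.5 yields all four cells of Table 2.

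**The case against.** **The trial will enrol 12 services, not ten.** This stands in part. At f = 0.75, 12 services still give 88.5–88.9% for 30% to 15%. They do not hold 78% for 20% to 10% at that share (73.4–77.1%), and nothing in the article ties the two extra services to re-testing loss. A reader might infer that the trial does not have 88% power. The article does not support that, because it gives no re-testing share; it supports only that the power is not ensured.

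**An allowance may be present but unreported.** It cannot be excluded, since some one-sided settings match at n of about 17 to 20. But none is stated, and the printed inputs yield 22.5.

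**Each service is its own control.** A between-year correlation would raise power. With an assumed correlation ρ of 0.5, subtracting 2ρk²p0p1 from V in setting A gives 93% for ten services at f = 1, 86% at 0.75, 73% at 0.50 and 53% at 0.30 (30% to 15%). The table is therefore not a most favourable case. Pairing softens the fall but does not remove it, and no correlation is given.

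**150 tested is a minimum.** True, but the Statistical analysis section draws the comparison from the 150 patients tested each year, so surplus testing may not count.

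**The treated share in the Background is weak evidence.** It describes past programmes for any STI and is not a trial assumption. It is used here only to show that loss is plausible.

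**The entry criterion.** A reader might see a conflict between services eligible "with a CT and NG positivity of at least 10" per cent and the assumed 15%. There is none: the first is a floor for each service, the second an expected prevalence. The modelled prevalences in the Background (11.9% CT, 7.1% NG) combine to 1 − 0.881 × 0.929 = 18% if independent, so 15% is not evidently optimistic.

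**Incentives and site reports address re-testing in both phases.** They do, and they should help. They support re-testing but do not put a figure for it into the power calculation.

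**Conclusion.** The point holds for what the article states. The printed inputs carry no loss between infection and re-test, the outcome requires treatment and re-testing, and the printed power at ten services is what full retention gives under settings A and B. A guarantee is therefore not justified.

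The shortfall is a range. With ten services, power for the larger and smaller effect is about 82–83% and 66–70% at 75% treated and re-tested, 69–73% and 51–58% at half, and 51–58% and 35–43% at 30%. Twelve services keep 88% for the larger effect down to roughly 71–73% retention, and 78% for the smaller down to roughly 78–86%.

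These figures rest on 5% alpha, the two settings shown and independence between years. The re-test share, alpha, sidedness, CV and between-year correlation are not in the article. Stricter two-sided settings lower the figures and pairing raises them; in every setting, power falls as fewer infected patients are treated and re-tested.

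**What to change.** In the Sample size section:

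1. State the assumed share of infected patients treated and the assumed share of those re-tested, together with alpha, sidedness, the CV used and any between-year correlation. If an allowance was already made, say so and give it.
2. Replace the sentence giving 88% and 78% with a short table of power by number of re-tested infections per service-year (for example at 30%, 50%, 75% and 100% of 22.5), for 10 and 12 services and for both effects.
3. Delete the word *ensure*.

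The re-tested percentage that is already reported to sites then shows which row of the table the trial is on. The cost is wording and one table, with no added services and no change to design or analysis. The downside is that the stated power will look less favourable.

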The overall aim of the TTANGO trial is to measure the clinical effectiveness, cost-effectiveness and cultural and operational acceptability of POC testing for CT and NG infections in remote Aboriginal communities. The primary objective is:

1. To determine whether the addition of POC testing to standard diagnostic procedures significantly decreases rates of repeat positive infections at three months among people with CT or NG infection in remote communities.

The secondary objectives are to determine:

1. Whether the addition of POC testing to standard diagnostic procedures significantly increases the proportion of CT and NG infections treated within seven days of specimen collection;

2. The cultural acceptability of POC tests to patients.

3. The operational acceptability to health service staff in remote community settings.

4. The cost effectiveness of the addition of POC testing to standard diagnostic procedures in remote primary health care services.

5. The diagnostic performance characteristics (sensitivity, specificity and positive and negative predictive value) of the POC test in a field setting compared to conventional laboratory testing.

6. A best practice model for quality management of STI/POC testing in remote health services.

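### The stated power for ten services (88% and 78%) and Table 2 do not follow from one set of assumptions, and 78% is not reached if the test is two-sided 5%

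*Protocol article*

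**What the plan says.** All of this is in the protocol article, Methods, Sample size.

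- **Inputs.** The article assumes that the "prevalence of CT and/or NG will be 15% at recruitment to the trial in each year", that "at least 150 patients aged 16–29 years will be tested at each health service" in both years, and "that 30% of patients will have a positive re-test within three months" under standard practice.
- **Method.** It cites one method for paired binary comparisons and one "for community randomised trials". It does not say how the two were combined.
- **Table 2 (30% to 15%).** The table is introduced as covering "differing community coefficients of variation (0.25, 0.30) and equal numbers of health services in each arm". At CV 25% it gives 8 services for 80% power and 10 for 90%. At CV 30% it gives 10 and 14.
- **Power sentence.** "At least ten services will provide data in both the intervention and control arms", which is said to secure 88% power for 30% to 15% "and 78% power to detect a reduction from 20% to 10"%. No CV is attached to either figure.
- **Test level.** No alpha or sidedness is stated anywhere. The primary objective in the Background asks whether POC testing "significantly decreases rates of repeat positive infections at three months among people with CT or NG infection", which names a direction but does not settle sidedness.

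**The concern.** Table 2 lists ten services twice, at 90% power (CV 25%) and at 80% power (CV 30%). The text gives 88% for ten services, which is neither entry, and adds a 78% for a second scenario that the table does not cover. The reader cannot tell which CV or test level lies behind the two powers, or whether table and text come from the same calculation.

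The adequacy of ten services, and the description of 12 as conservative, rest on these figures. If the powers came from a more lenient test than the table, or than the test eventually used, the 20% to 10% scenario is weaker than the text suggests.

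**Working it through.** **Inputs.** n = 150 × 0.15 = 22.5 infected per service-year, all counted as re-tested. CV k = 0.25 or 0.30. Number of services c = 10. Alpha is not given, so one-sided 5% (z = 1.645) and two-sided 5% (z = 1.960) are both tried.

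**Formula** (cluster formula with a coefficient of variation):

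c = a + (z_alpha + z_beta)² × V / (p0 − p1)²,

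V = p0(1 − p0)/n + p1(1 − p1)/n + k²(p0² + p1²).

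Here a is the small-sample addition: 0 (none), 1 (unmatched) or 2 (paired). Power at c services is Φ(√[(c − a)(p0 − p1)²/V] − z_alpha).

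**Variance terms.**
- 30% to 15%: V = 0.21/22.5 + 0.1275/22.5 + k² × 0.1125 = 0.0220 (k = 0.25) or 0.0251 (k = 0.30). Divided by 0.15² this is 0.979 or 1.117.
- 20% to 10%: V = 0.16/22.5 + 0.09/22.5 + k² × 0.05 = 0.0142 or 0.0156. Divided by 0.10² this is 1.424 or 1.561.

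**Step 1: reproduce 88% and 78%.** At one-sided 5%, a = 1, k = 0.30:
- 30% to 15%: √(9/1.117) − 1.645 = 1.194, power 88.4%.
- 20% to 10%: √(9/1.561) − 1.645 = 0.756, power 77.5%.

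These round to the stated pair. With a = 0, 1 or 2 at n = 22.5, no other combination does. The nearest is one-sided, a = 2, k = 0.25, with 88.8% and 76.6%.

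**Step 2: put that setting into Table 2, CV 30% row.**
- 80% power: 1 + (1.645 + 0.842)² × 1.117 = 7.9 services. The table prints 10.
- 90% power: 1 + (1.645 + 1.282)² × 1.117 = 10.6 services. The table prints 14.

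Rounding does not close the gap: rounded up to even, these are 8 and 12. At 12 services this setting already gives 93%.

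**Step 3: look for a setting that gives the whole table.** Services needed for 30% to 15% at n = 22.5:

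| Test | a | CV 25%: 80% / 90% | CV 30%: 80% / 90% |
|---|---|---|---|
| One-sided | 0 | 6.1 / 8.4 | 6.9 / 9.6 |
| One-sided | 1 | 7.1 / 9.4 | 7.9 / 10.6 |
| One-sided | 2 | 8.1 / 10.4 | 8.9 / 11.6 |
| Two-sided | 0 | 7.7 / 10.3 | 8.8 / 11.7 |
| Two-sided | 1 | 8.7 / 11.3 | 9.8 / 12.7 |
| Two-sided | 2 | 9.7 / 12.3 | 10.8 / 13.7 |
| **Table 2** | | **8 / 10** | **10 / 14** |

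Rounding up, up to even, to nearest, or to nearest even, no line gives 8, 10, 10 and 14 together. Each row can be matched alone. For example, one-sided with a = 1 rounds up to 8 and 10 at CV 25%, and two-sided with a = 1 rounds up to even at 10 and 14 at CV 30%.

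**Step 4: power of ten services if the test is two-sided 5%.**

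| a | 30% to 15%, CV 0.25 / 0.30 | 20% to 10%, CV 0.25 / 0.30 |
|---|---|---|
| 0 | 89.2% / 84.9% | 75.5% / 71.6% |
| 1 | 85.8% / 81.0% | 71.0% / 67.0% |
| 2 | 81.6% / 76.3% | 65.9% / 61.9% |

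The highest value for 20% to 10% is 75.5%. Rounding n up to 23 raises it to 76.2%.

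**Step 5: the 12 services enrolled, two-sided 5%, a = 1.** 30% to 15%: 91.8% / 88.1%. 20% to 10%: 79.4% / 75.6%.

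**The case against.** The strongest reply is that the article fixes neither alpha nor sidedness. A reader who assumes two-sided 5% might infer that 78% is unattainable at either CV, or that the two powers contradict each other. The document does not support that: at one-sided 5%, with a CV the plan itself uses, both figures appear together (step 1).

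Nor is 88% a contradiction on its face. It lies between the table's 80% and 90% for ten services, and its CV is not stated. Rounding could also link it to the CV 25% row: one-sided with a = 2 needs 10.4 services for 90%, which rounds to 10 and gives 88.8% at ten. A condensed article may also leave the choice of alpha to the full protocol.

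Two further inferences should be resisted. One is that the CV 25% row ought to read 10 and 12. That presumes a two-sided test and a rounding rule that the article does not state. The other is that the paired-binary reference is misplaced. The article does not say whether the same patients recur in both years, and the endpoint is a within-service difference.

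What remains is that neither rescue carries over to the rest of Table 2. The one-sided, CV 0.30 setting fails the CV 30% row. The one-sided, a = 2 reading rounds to 9 and 12 in that row, against 10 and 14, and gives 76.6% rather than 78%. These are disagreements among printed figures, not omitted detail.

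On consequence the reply has weight: 12 services are enrolled and 150 is a minimum, so the main scenario stays at 88% or better in step 5.

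**Conclusion.** The point holds in a limited form. On the plan's inputs and the cluster formula, the power sentence and Table 2 cannot both be right, and none of the alpha, addition and rounding choices tried yields all four table cells. The only setting of this formula that returns 88% and 78% together implies about 8 and 11 services where the table has 10 and 14.

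If the test is two-sided 5%, ten services give 82% to 89% (CV 0.25) or 76% to 85% (CV 0.30) for 30% to 15%. For 20% to 10% they give 66% to 76% or 62% to 72%. The stated 78% is then too high by about 2 to 16 points. That shortfall is conditional on the two-sided assumption; the inconsistency between text and table is not.

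The figures rest on 22.5 infected per service-year, all re-tested. Testing more than 150 would raise the power. Incomplete re-testing would lower it, and the Discussion says repeat positivity is calculated among those re-tested.

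**What to change.** Recompute Table 2 and the power sentence together, with one formula, one declared alpha and sidedness, one small-sample addition and one rounding rule. Attach the CV to each power, and replace the assurance of 88% with the range over CV 0.25 to 0.30.

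As an example, at two-sided 5% with the one-cluster addition (CV 0.25 / 0.30):
- ten services: 86% / 81% for 30% to 15%, and 71% / 67% for 20% to 10%;
- the 12 services enrolled: 92% / 88% and 79% / 76%.

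If a one-sided test or the paired addition was intended, say so and give the matching figures. The change is to wording and a small table, with no change in the number of services. Its cost is a less favourable stated power, chiefly for 20% to 10%.
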